#### Consent

Study researchers will provide eligible staff and patients with information leaflets and consent forms. Staff and patients will sign a consent to participate in interviews or focus groups. Staff will complete a separate consent form to complete questionnaires at study cessation.

#### Economic evaluation

The economic component of the study will consist of a cost analysis of the trial and budget impact analysis of the strategy. Concurrent with the pilot trial, data collected will be employed in a cost-analysis to establish the cost of delivering the strategy compared to the control (calculated as per national guidelines [67]). Appropriate one-way sensitivity analyses will be conducted around key parameters to investigate parameter uncertainty. In addition, a budget impact analysis (BIA) will be conducted in line with national guidelines [68] to predict the potential financial impact of the adoption and diffusion of the intervention in the short term (up to 5 years as per HIQA guidelines). The results of these economic analyses used to inform decisions regarding resource or budget planning for a definitive trial.

### Analysis

#### Quantitative analysis

As this is a pilot trial, the analyses will focus on describing the key process measures to decide if the main trial is feasible and desirable. Descriptive analyses will be conducted for the primary outcomes; however, this will be treated as exploratory. Using anonymised audit data, a baseline table (descriptive statistics and frequencies) will compare the demographic and clinical characteristics of the intervention and control groups. Descriptive summaries will be generated for the patient outcome, screening intention and attendance. The data will provide information on the parameters for an accurate sample size calculation (mean, standard deviation and intervention effect) for the future definitive trial. Descriptive analysis will be conducted to assess practice recruitment and retention rates, and reach. All data will be managed and analysed using Stata V14 software.

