### Study design

IDEAs is a cluster randomised pilot trial [49], with an embedded process evaluation and a partial economic evaluation (cost analysis). Eight general practices (clusters) will be randomly allocated to intervention (*n* = 4) or waitlist control (*n* = 4) groups following stratification by practice size. Practices in the wait-list control group will be offered access to the intervention material and support the following pilot trial completion at 6 months. Data from the trial will be analysed and reported in accordance with the CONSORT criteria. The results of the pilot trial will inform the design of a large cluster randomized trial that will be powered to test the effectiveness of the intervention on DRS uptake. Continuation criteria, based on quantitative and qualitative process evaluation data, will be used to inform the decision about whether the intervention should be further evaluated as part of a full-scale randomised controlled trial (Table 1).

**Table 1 Tab1:** Summary of continuation criteria

^a^Continuation criteria	Measures used	Assessment of whether criteria have been met
Feasibility to recruit and retain practices.	• Number of practices responding to a call for Expression of Interest^b^ • Practice retention rates	If > 50 general practices within 2 months respond to call, then it is likely to proceed to full trial (*green*). If < 40 practices respond to call, then progression is unlikely to be feasible (*red*). If 40–50 practices respond within 2 month, then the Trial Steering Committee (TSC) will consider the feasibility of proceeding to the full-scale trial (*amber*) based on taking steps to improve response rate. If 8 practices are retained throughout a 6-month intervention period, then it is likely to proceed (*green*). If < 5 practices are retained, then a full-scale trial is unlikely to be feasible (*red*). If 5–7 practices are retained throughout the intervention period, then the TSC will consider feasibility of proceeding (*amber*) based on taking steps to improve retention.

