Intervention has potential effect on screening uptake and demonstrates potential cost savings which are likely to outweigh the direct cost of implementing the intervention; specifically, the intervention (1) increases the absolute number of patients registered for diabetic retinopathy screening and (2) increases the absolute number of patients attending or intending to attend screening, measured descriptively	• Number registered for diabetic retinopathy screening based on practice audit data • Number attending or intending to attend based on practice audit data • Potential savings calculated based on cost of delivering intervention compared to control, and absolute increases in number attending or intending to attend	The TSC will judge whether the intervention has some positive impact and demonstrates cost savings.

^a^Continuation criteria are in place to facilitate the Trial Steering Committee (TSC) to assess whether it would be viable to progress to a full trial or whether this could be done following modifications to the trial protocol [50]. Continuation to the full trial will not occur unless problems can be overcome. Continuation criteria may be adapted, and supplementary data may be used to facilitate decision-making about whether to proceed to a full trial even when criteria have not been met

^b^To achieve 80% power to detect a change from 60 to 70% (*α* = 0.05), a total sample of 712 eligible patients would be needed. Assuming an average practice size of 1200 patients and a 5% prevalence of type 2 diabetes, at each practice, it is estimated that 12 patients would not be registered for the screening programme (20%). Of the 48 patients registered, 18 would be eligible (17 would be non-consenters (34%) and 1 would be a non-attender (3%)). Therefore, at least 40 practices would need to be recruited (20 per arm) for a full trial. To allow for a lower number of eligible patients per practice, we aim to recruit > 40 practices for the full trial

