### Outcomes

Primary outcome measures will be the following:
Patient registrationPatient response to reminders: (a) *intention* to contact RetinaScreen, (b) have contacted RetinaScreen, (c) have attended a screening or (d) none of these. This will be verified through a phone call from the practice as part of the 6-month audit.Patient attendance at retinopathy screening, verified through a letter received by practices from the national screening programme, RetinaScreen. Patient attendance will be measured (via practice audit) at baseline and at 6 months.

Figure 3 shows the schedule of enrolment, interventions and assessments.

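### The pilot is said to supply inputs for an accurate sample size calculation, but the listed inputs do not fit categorical outcomes in a cluster trial, and four practices per arm cannot estimate the effect precisely enough to plan on

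*Protocol article*

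**What the plan says.** Under Quantitative analysis, the article says the pilot will provide information on the "parameters for an accurate sample size calculation (mean, standard deviation and intervention effect) for the future definitive trial". The same paragraph calls the analysis of the primary outcomes descriptive and exploratory.

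The Outcomes section lists three patient outcomes: registration (yes or no); response to reminders, with categories that include "have contacted RetinaScreen, (c) have attended a screening or (d) none of these"; and "Patient attendance at retinopathy screening, verified through a letter received by practices from the national screening programme" (yes or no). None is continuous.

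The pilot and its successor are both cluster randomised. For the pilot, "Eight general practices (clusters) will be randomly allocated to intervention (*n* = 4) or waitlist control (*n* = 4) groups"; for the successor, "The results of the pilot trial will inform the design of a large cluster randomized trial". The number eight was set by resources (Recruitment of general practices).

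Footnote b to Table 1 sketches the definitive trial: for "80% power to detect a change from 60 to 70" per cent at alpha 0.05, "a total sample of 712 eligible patients would be needed". At 18 eligible patients per practice it concludes that at least 40 practices are needed, 20 per arm. No ICC, between-practice variance or design effect appears anywhere in the article.

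**The concern.** There are three separate difficulties with the one sentence.

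1. **The parameters do not match the outcomes.** For a yes/no outcome the patient-level SD is fixed by the proportion and adds nothing. The article's own calculation for the definitive trial works in proportions.
2. **The cluster parameter is missing.** A cluster trial cannot be sized without an ICC or an equivalent between-practice variance. Footnote b leaves it out, and the list of what the pilot will supply leaves it out again.
3. **The intervention effect is named as an input to an accurate calculation.** A difference between four practices and four practices carries so much sampling and between-practice variation that it cannot serve this purpose.

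What is at stake is the definitive trial, not the conduct of the pilot. If the listed inputs were used as they stand, the later trial could be sized with no allowance for clustering and on an observed effect that is too large or too small by chance.

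**Working it through.** **Inputs from the article.** 60% v 70%, 80% power, alpha 0.05, 712 patients, 40 practices (footnote b to Table 1); four practices per arm (Study design); 18 eligible patients per practice, plus 12 not registered (Sample size). Because registration is itself an outcome and the inclusion criteria cover anyone eligible for the programme who has not attended, 18 + 12 = 30 per practice is used as a second case.

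**Assumptions.** The article gives no ICC, so 0 to 0.10 is assumed. Pilot uptake is taken as 20% or 50% in both arms, or as the article's 60% v 70%. Cluster sizes are taken as equal.

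**Step 1: reproduce footnote b.** The article does not state sidedness; a two-sided test with pooled variance reproduces the figure.

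n per arm = [1.960 × √(2 × 0.65 × 0.35) + 0.842 × √(0.6 × 0.4 + 0.7 × 0.3)]² / 0.10² = 355.9, so 356 per arm and 712 in total. Then 712 / 18 = 39.6, so 40 practices. Both figures match, and they match only with a design effect of 1.

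**Step 2: what the missing ICC is worth.** Design effect DE = 1 + (18 − 1) × ICC; practices per arm = 356 × DE / 18, rounded up.

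| Assumed ICC | DE | Practices per arm | Power with 20 per arm |
|---|---|---|---|
| 0 | 1.00 | 20 | 80% |
| 0.02 | 1.34 | 27 | 68% |
| 0.05 | 1.85 | 37 | 54% |
| 0.10 | 2.70 | 54 | 40% |

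**Step 3: precision of the pilot difference.** SE = √{[p₁(1 − p₁) + p₂(1 − p₂)] × DE / (4m)}, with m patients per practice and DE = 1 + (m − 1) × ICC. The half-width is 2.447 × SE (t, 8 − 2 = 6 degrees of freedom). Example: m = 18, ICC 0.05, 60% v 70%: SE = √(0.45 × 1.85 / 72) = 0.1075; half-width 0.263.

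Half-widths in percentage points:

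| m | ICC | 20% both arms | 50% both arms | 60% v 70% |
|---|---|---|---|---|
| 18 | 0 | 16.3 | 20.4 | 19.3 |
| 18 | 0.02 | 18.9 | 23.6 | 22.4 |
| 18 | 0.05 | 22.2 | 27.7 | 26.3 |
| 18 | 0.10 | 26.8 | 33.5 | 31.8 |
| 30 | 0 | 12.6 | 15.8 | 15.0 |
| 30 | 0.02 | 15.9 | 19.9 | 18.8 |
| 30 | 0.05 | 19.8 | 24.7 | 23.5 |
| 30 | 0.10 | 25.0 | 31.2 | 29.6 |

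Every entry exceeds 10 points.

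**Step 4: what planning on a chance effect would do.** With SE 0.1075, a true 10-point difference would appear as 20 points or more with probability 1 − Φ(0.10 / 0.1075), about 18%, and as zero or less equally often (normal approximation). Planning on 60% v 80%:

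n per arm = [1.960 × √(2 × 0.7 × 0.3) + 0.842 × √(0.24 + 0.16)]² / 0.20² = 81.2, so 82 per arm against 356.

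If the truth were still 60% v 70%, power with 82 per arm would be Φ{[0.10 × √82 − 1.960 × √0.455] / √0.45} = Φ(−0.62), about 27%, before any loss to clustering.

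**Step 5: can the pilot supply the ICC?** Only roughly. In 20,000 beta-binomial simulations of eight practices of 18, with a within-arm ANOVA estimator and a true ICC of 0.05, 95% of estimates lay between −0.04 and 0.18.

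**The case against.** The strongest reply is that the sentence promises little. It says the data will provide information on parameters, and the Study design section says only that results will inform the later design. Footnote b already fixes 60% to 70% as the planning difference, and nothing says the pilot estimate will replace it. This stands. A reader might infer that the definitive trial *will* be sized on the pilot's observed effect and without an ICC. The article does not say so, and the mis-sizing in step 4 is therefore conditional.

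Second, a mean and SD can be valid planning inputs in a cluster trial if they describe practice-level uptake, since the between-practice SD carries the information an ICC expresses. That also stands as a possible reading, so it would be too strong to call a mean and SD plainly wrong. But the article does not state this reading, and it presents the outcomes at patient level.

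Third, some inputs are already covered. Table 4 says recruitment and retention rates will inform the later sample size, the number of eligible patients per practice is recorded, and control-arm status at 6 months is extracted. This is right, and retention needs no addition.

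Fourth, a condensed article may leave the choice of variance parameters to a fuller document, and a pilot needs no formal sample size. Both are fair. The point here is not the pilot's size or a missing detail. It is that the article names a list, calls the resulting calculation accurate, and includes in that list an effect the design cannot estimate to that standard.

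**Conclusion.** The point holds as a fault in what the article states. The listed parameters are not the natural ones for binary or categorical outcomes, the list omits the clustering parameter that footnote b also lacks, and the accuracy claimed is a property the design does not have. The half-width for the difference is about 16–34 points with 18 eligible patients per practice and 13–31 with 30, against a 10-point target. These ranges rest on assumed ICCs of 0 to 0.10, assumed uptake of 20–50% or 60% v 70%, equal cluster sizes and 6 degrees of freedom.

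The harm arises only if the observed effect is used for planning; the example then cuts the trial from 356 to 82 per arm. No pilot data collection or continuation criterion is affected. The change should be made before the pilot results are used for planning.

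**What to change.** In Quantitative analysis, replace the parenthesis with:

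- control-arm uptake at 6 months;
- the ICC, or the between-practice SD of uptake, with its interval, to be read alongside an external range because eight practices estimate it poorly;
- the mean and variation of the number of eligible patients per practice.

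Delete *accurate*. Add one sentence saying that the definitive trial will be sized on a prespecified worthwhile difference, such as the 10 points in footnote b, and not on the difference observed in the pilot.

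The cost is a change of wording and one extra estimate from audit data already collected, provided that the merged anonymised file keeps a practice identifier.

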#### Qualitative analysis

All focus groups and interviews will be digitally recorded and transcribed verbatim. Transcripts will be entered into the NVivo qualitative analysis software to facilitate data management, coding and retrieval. Transcripts will be coded using the Framework Method [69], drawing on existing frameworks. For example, FRAME will be used to code modifications to the intervention; specifically, the *process* of modification (what was modified, at what level, who decided to make the modification, the nature of the modification, when it occurred, whether it was planned and whether it was fidelity-consistent or inconsistent) and the *reason(s)* (socio-political, organisational, provider, recipient). The framework approach is suitable for projects with prespecified objectives such as evaluating acceptability and feasibility. It also allows researchers to develop unexpected themes during initial phases of familiarisation and open coding and facilitates cross-group comparison allowing us to examine themes among different types of practices and patients.

#### Integration

Where available, quantitative and qualitative data will be integrated to ensure a comprehensive, multi-perspective approach to exploring the intervention process. Table 5 outlines which data will be integrated for different constructs. For example, findings from the qualitative analysis will be integrated with quantitative data to assess fidelity, feasibility and acceptability [70]. Quantitative and qualitative data collected on intervention delivery will be classified according to existing frameworks for coding adaptation and modifications to interventions [65, 66].

**Table 5 Tab5:** Summary of data integration

Research question	Implementation outcome	Data
**Intervention**		
1. Are the intervention content, delivery and procedures acceptable to people with diabetes who will receive it, and staff who will deliver the intervention?	Acceptability	**Quantitative:** staff questionnaires **Qualitative:** staff and patient interviews or focus groups; any feedback on intervention content during the study
2. Is the intervention feasible to deliver in primary care practice and is fidelity achieved?	Feasibility	**Quantitative:** staff questionnaires, number and type of staff who attend briefing, role assignment, time and resource use **Qualitative:** staff interviews, any feedback on intervention during the study
	Fidelity & adaptations	**Quantitative:** number of patients eligible to receive the intervention and number of reminders delivered, number and type of staff who attend briefing
		**Qualitative:** staff and patient interviews and focus groups data on any changes to role in intervention delivery and the reason for the change, any changes to the intervention protocol.
3. What are the costs associated with the intervention?	Costs	**Quantitative:** number and type of staff who attend briefing, role assignment, time and resource use

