## Aims and objectives

The main aim of the IDEAs (Improving Diabetes Eye screening Attendance) study is to investigate the feasibility of a multifaceted implementation intervention in primary care to improve the uptake of the national DRS programme, RetinaScreen. The intervention was developed through a multi-stage process, combining theory, consultation with multiple stakeholders and existing evidence. In line with Medical Research Council guidance [31], the study will address uncertainties about feasibility, economic evaluation and the study procedures. Specifically, it will address the following questions:
Are the intervention content, delivery and procedures acceptable to people with diabetes who will receive it and staff who will deliver the intervention?Is the intervention feasible to deliver in primary care practice and is fidelity achieved (i.e., intervention delivered as intended)?Are the data collection processes, including mode and duration of data collection and outcome measures used, acceptable to staff?Is the study feasible in terms of recruitment and retention procedures and data collection?What are the costs associated with the intervention?Do the results suggest that the intervention increases the uptake of DRS?

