Intervention is implemented as planned; that is, audit and feedback, addition of electronic prompts and delivery of a reminder in any format and receipt of intervention by eligible population of people with diabetes in participating practices	• Exploration of implementation fidelity during practice staff and patient interviews • Practice self-report during research support phone calls • Percentage of eligible patients receiving intervention based on practice audit data	If all core intervention components (audit, prompts, reminders) have been delivered by > 75% of practices, then it is likely to proceed to full trial (*green*) subject to review of qualitative data. If < 50% have delivered components, then it is unlikely to proceed (*red*). If 50–75% have delivered core components, then the TSC will consider the feasibility of proceeding (*amber*). The TSC will consider both the quantitative and qualitative data to judge whether the intervention is has been implemented.
Intervention is acceptable to patients and practice staff	• Percentages of staff reporting acceptability of intervention on self-report questionnaire. • Issues regarding acceptability of the intervention explored in qualitative interviews with staff and patients	If the intervention is acceptable to > 75% practice staff, then it is likely to proceed to full trial subject to review of qualitative data (*green*). If intervention is acceptable to < 50% staff, then it is unlikely to proceed (*red*). If the intervention is acceptable to 50–75% staff, then TSC will consider feasibility of proceeding (*amber*). The TSC will consider the quantitative and qualitative data and make an overall judgement on whether the intervention is acceptable.

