##### Verbal reminders

All eligible patients will receive a phone call from a practice nurse, reminding them to attend the screening. Nurses who deliver the phone call will follow a short script (Additional file 2) and inform the patient they will receive a follow-up letter with more information. At this point, the patient status will also be updated on the audit file and electronic patient record, for example, if the patient is attending another service for screening (e.g., ophthalmologist). This will enable staff to shortlist patients who should receive the letter. In-person reminders will be delivered opportunistically by GPs and practice nurses if an eligible patient attends for an appointment during the 6-month trial period. They will follow the short script (Additional file 2) and provide patients with a standard information leaflet (Additional file 3).

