### Data collection

In line with the Medical Research Council guidance [31], a mixed methods approach will be used, involving data collection at the practice, professional and patient level, to assess implementation outcomes, as defined by Procter et al. [58], namely appropriateness, acceptability, feasibility, reach/penetration, fidelity and costs (resource use). A summary is provided below (Table 3) with more detail and definitions available in Table 4.

**Table 3 Tab3:** Summary of data collection

Practice level	
• **Audit;** ongoing data collection (i.e., number of eligible patients, number of reminders delivered) [reach, fidelity]	
• **Research processes;** data collection at study start (i.e., recruitment and retention, briefing attendance and feedback), and via monthly phone calls to practices (i.e., role assignment, changes to the intervention protocol, time and resource use, any feedback) [feasibility, fidelity, costs (resource use)]. Information collected will vary according to timing of the phone call. For example, during the first phone call, the time taken to conduct the audit will be recorded; during the second call, the time needed to deliver reminder phone calls will be recorded***.***	
Professional	
• **Staff questionnaires** at study cessation [appropriateness, acceptability and feasibility]	
• **Staff interviews** at study cessation [acceptability, feasibility and fidelity]	
Patient	
• **Patient interviews or focus groups**, at study cessation [acceptability and fidelity]

**Table 4 Tab4:** Data collection conducted as part of the process evaluation

**Data items**	**Timing**	**Outcome(s)**					
		**Appropriateness**^**b**^	**Acceptability**^**b**^	**Reach**^**b**^	**Feasibility**^**b**^	**Fidelity**^**b**^	**Costs**^**a**^
**Source:** Audit data **Level:** Patient **Content:**				✓		✓	
• Number of patients eligible to receive the intervention	Baseline						
• Number of phone reminders; record on the audit file that (a) patient phoned (and date), (b) spoke to the patient and (c) delivered the scripted message.	On-going						
• Number of letter reminders	On-going						
• Number of in person reminders; review patient files and record whether the electronic alert has been deleted. Deleting the electronic alert will be taken to indicate that the intervention was delivered (self-report).	At 6 months						
**Source:** Research processes **Level:** Practice **Content:**					✓	✓	✓

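### In-person reminders: an alert still in place at month 6 cannot separate a prompt staff did not act on from a patient who never attended

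*Protocol article*

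**What the plan says.** Under Verbal reminders, the protocol article makes the face-to-face component conditional on a visit: "In-person reminders will be delivered opportunistically by GPs and practice nurses if an eligible patient attends for an appointment during the 6-month trial period". The phone call, by contrast, is due to every eligible patient. The patient's status is updated at the call, and the article says of this step: "This will enable staff to shortlist patients who should receive the letter".

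Table 4 has one block of audit items, ticked for both reach and fidelity. Its only patient-level denominator is "Number of patients eligible to receive the intervention", taken at baseline. Phone, letter and in-person reminders are separate items. In-person reminders are counted at 6 months by checking whether the alert on the patient's record has been deleted, and deletion is taken as delivery. The quantitative entry for fidelity in Table 5 lists the "number of patients eligible to receive the intervention and number of reminders delivered", together with staff attendance at the briefing.

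Under Remind clinicians, action or inaction on the alert is captured where the GP software can already do so. The Discussion adds that software will not be modified for this purpose, and that alerts may be deleted without the reminder having been given.

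**The concern.** The second research question asks whether fidelity is achieved, meaning delivery in the intended way. For the in-person component, that means a reminder at a visit, if there is a visit. A measure that does not know whether a visit occurred mixes staff behaviour with patient behaviour.

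The two explanations for a low figure call for different refinements before a definitive trial. If staff pass over the prompt, the prompt or the training needs attention. If patients do not come in, the opportunistic route has limited reach in this group however well staff perform. Differences between practices in visit rate could also be read as differences in fidelity.

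**Working it through.** **No stated figure.** The article gives no fidelity formula, fidelity figure or consultation rate, so there is nothing to reproduce. The check is of what the listed items can distinguish.

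**States of the alert at month 6.** Leave aside deletion without delivery, which the Discussion already acknowledges.

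| Patient consulted after prompt? | Staff acted? | Alert at month 6 | Fidelity failure? |
|---|---|---|---|
| Yes | Yes | Deleted | No |
| Yes | No | Present | Yes |
| No | Not applicable | Present | No |

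The last two rows give the same record. The items listed under the trial's Data collection heading and in Table 4 (demographic and diabetes items, screening status and intention, reminder counts) contain nothing that separates them.

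**Size.** Let *v* be the share of eligible patients with at least one GP or nurse consultation while the prompt is active, and *f* the share of those who are given the reminder. The only in-person percentage the listed items allow is delivered / eligible = *f* × *v*.

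Inputs:
- Eligible patients per practice, from Sample size: 48 × (0.34 + 0.03) = 17.76, which the article rounds to 18. Four intervention practices give 4 × 18 = 72.
- *v* from 0.5 to 0.9. This is an assumption; the article gives no value.

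Results:
- Perfect delivery, *f* = 1: 0.5 × 72 = 36 to 0.9 × 72 = 64.8, about 65 patients, shown as 50-90%.
- *f* = 0.8: 0.8 × 0.5 = 40% to 0.8 × 0.9 = 72%.

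The percentages do not depend on the count of 18. Adding the 12 unregistered patients per practice (12 + 18 = 30) would leave them unchanged.

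**Two practices with the same figure.** With 18 eligible patients each, suppose that in practice A nine consult and all nine are reminded, and that in practice B all 18 consult and nine are reminded. Both show 9/18 = 50%. Per opportunity, A has 9/9 = 100% and B has 9/18 = 50%.

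**Other formats.** A call is due to all eligible patients, so the baseline-eligible denominator is right for phone. For letters, the post-call status is written to the audit file, so the patients who should have received one can be recovered. The problem is confined to the in-person component.

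**The case against.** The strongest counter-argument is that no fidelity ratio is prescribed. Table 5 is introduced with the words "Table 5 outlines which data will be integrated for different constructs": it lists sources and defines no estimator. Fidelity also draws on briefing attendance, monthly calls, and staff and patient interviews. The article is condensed and refers to an audit manual that is not shown. Personal audit files stay in the practice, so a visit check remains possible there.

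Much of this stands. In particular, a reader might infer that fidelity is calculated as reminders over all baseline-eligible patients, so that a fully adherent practice is marked as under-delivering. The documents do not support that:

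- The only fidelity rule with thresholds, in Table 1, takes the practice as its unit and rests on "delivery of a reminder in any format and receipt of intervention by eligible population of people with diabetes in participating practices", with qualitative review by the Trial Steering Committee. Every eligible patient is due a call, and after three failed attempts the letter is issued. A fully adherent practice therefore gives everyone a reminder in some format, whatever the visit rate.
- A pooled ratio of reminders to eligible patients would exceed 1 under perfect delivery. Assume phone contact of 60-100%, 0-20% of those contacted screened elsewhere, and 20-80% visiting. The ratio then runs from 0.60 + (1 − 0.60 × 0.20) + 0.20 = 1.68 to 1.00 + 1.00 + 0.80 = 2.80.
- Table 1 also lists the percentage of eligible patients receiving the intervention, but gives it no threshold.

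What the counter-argument does not remove is the ambiguity of the in-person item. Table 4 is offered as the more detailed account of data collection, and it says how this item is measured. An analysis plan can choose a denominator but cannot use a variable that was not recorded. Researchers receive files already anonymised at the practice, so they could not add it themselves; practices would have to reopen records. Interviews and monthly calls may help to explain a low figure but do not give a count.

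**Conclusion.** The point holds for the in-person component only. Alert deletion measured against baseline eligibility can describe in-person reach. It cannot show in-person fidelity, because absence of a visit and failure to act leave the same record except where the software already logs inaction. On the assumed 50-90% consultation share, perfect delivery would appear as 50-90% of eligible patients. The range is only as good as that assumption, and it takes alert deletion to be an accurate record of delivery.

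No continuation threshold in Table 1 depends on this figure. The consequence is for interpretation: the in-person part of the second research question could not be answered quantitatively, and the pilot's guidance on refining that component would be weaker. This is a modest but worthwhile improvement, not an error in a decision rule.

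**What to change.** Add one yes/no item to the month-6 audit file in intervention practices: any GP or nurse consultation between the date the prompt was added and month 6. It can be read from the record already open for the alert check.

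In Tables 4 and 5, separate the two in-person measures:
- reach = patients given an in-person reminder / all eligible patients;
- fidelity = patients given an in-person reminder / eligible patients who consulted.

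Phone and letter items can stay as they are. The cost is slightly more audit time, for about 18 patients per practice (72 over four practices) on the plan's figure, plus a short edit to the two tables. The item does not address alerts deleted without delivery, so that acknowledged limitation remains.
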